## Abstract

**Methods::**

This is a randomized, assessor-blind, and pragmatic pilot study. We will recruit 40 participants who want to stop smoking and randomly allocate them into an NRT group and an NRT + AA group with a 1:1 ratio. Participants will receive NRT for 4 weeks and the NRT + AA group will receive additional AA treatment with 5 AA points (Shenmen (TF4), lung (CO14), throat (TF3), inner nose (TG4), and endocrine (CO18)) twice a week for 4 weeks. Follow-up will be conducted 1 and 3 months after intervention completion. The primary outcome will be tobacco consumption and abstinence rate determined by calculating the rate of change in cigarette use and a urine test. Secondary outcomes will be the quality of life (EuroQol-5D and visual analogue scale), nicotine dependence (Fagerstrom test for nicotine dependence), nicotine withdrawal (Minnesota nicotine withdrawal scale), physical effects, satisfaction, and safety measurement (adverse events).

**Results::**

We will investigate the efficacy and safety of AA combined with NRT treatment for smoking cessation.

**Conclusion::**

Our study will provide additional clinical evidence for AA as an adjuvant treatment for smoking cessation.

**Trial registration number::**

Clinical Research Information Service (registration number: KCT0007212).

## 1. Introduction

Smoking is a major preventable public health threat.^[1]^ It causes 6 million direct deaths annually and has induced approximately 900,000 deaths from secondhand smoke. Although not clarified, the dangers of third-hand smoke have been raised.^[2]^ Globally, 25% of men and 5% of women smoke daily as of 2015,^[3]^ and it is reported that smoking requires more inpatient care than alcohol and illegal drug use combined.^[4]^ Researchers have focused on the deleterious effects on cancer, fertility, and respiratory and musculoskeletal system disease.^[5–7]^ Smoking increases insulin resistance and further causes metabolic syndrome and diabetes.^[8]^

Many smokers try to quit smoking. Of those attempting to quit without any treatment, 60% start smoking again within 2 weeks and only 5% succeed.^[9]^ Therefore, various treatments are administered, such as the medications bupropion and varenicline, which have proven efficacy through several randomized controlled trials.^[10]^ Nicotine replacement treatment (NRT) has doubled the successful smoking cessation rate.^[11]^ It is absorbed through the oral or nasal mucosa (via gum, Rosen, tongue, inhaler, or spray) or the skin, which differs from other products in that they absorb nicotine slowly and passively.^[12]^ NRT reduces motivation for smoking, prevents the physiological and mental withdrawal symptoms that occur during the cessation period, and stimulates the nicotine receptors and the release of dopamine in the ventral cortex of the brain.^[13]^

However, these treatments have some side effects such as nausea, insomnia, and headaches.^[14]^ Some drugs exhibit side effects such as anxiety, cravings, tension, dry mouth, dizziness, and sedation when used during the smoking cessation process.^[15]^ Acupuncture is 1 alternative method for smoking cessation. Inserting a needle in a specific place can correct the disturbance of a force known as qi. Also, acupuncture stimulates the nerves and connective tissue located throughout the body.^[16]^

Stimulating the auricular acupuncture (AA) point greatly influences the limbic system of the brain. This mechanism is mediated through the trigeminal and vagus nerves and the cervical flexus.^[17]^ In addition, when a smoker experiences withdrawal during smoking cessation, stimulating the ear can minimize these effects by controlling the release of dopamine and serotonin.^[18]^ According to studies from the United States and Norway, 40% of smokers successfully quit through AA,^[19]^ indicating that this treatment has a positive effect on decreasing smoking desire.^[20]^ In 1 study, adjuvant AA has resulted in more significant smoking cessation effects and stability than NRT alone.^[21]^

Regardless of this research, no randomized controlled trials focus on the effect of AA combined with NRT on smoking cessation. This study will investigate the efficacy and safety of adjuvant AA treatment on smoking cessation.

## 2. Methods

### 2.1. Objectives

This pilot study aims to assess the efficacy and safety of AA treatment combined with NRT for smoking cessation comparing NRT alone.

### 2.2. Ethics approval and registration

This study complied with the Helsinki Declaration and was approved by the Institutional Review Board (IRB) of Dongguk University Bundang Oriental Hospital (DUBOH 2022-0005; final version 1.1 on April 7, 2022) and registered in the Clinical Research Information Service (CRIS, KCT0007212) on April 19, 2022.

### 2.3. Design

This study is a randomized, assessor-blinded, pragmatic pilot clinical trial with 2 parallel groups. We intend to investigate the synergic effects of AA treatment on smoking cessation. Eligible participants will be assigned to 1 of 2 groups with a 1:1 ratio. The control group will receive only NRT, and the experimental group will receive AA treatment + NRT. The study period will include 4 week-treatment phase and 3 month-follow-up. The study design flowchart is as shown in Figure 1.

**Figure 1. F1:**
[figure not shown]
Flow diagram based on CONSORT 2010.^[22]^ AA = auricular acupuncture, NRT = nicotine replacement treatment.

### 2.4. Participants

We will recruit 40 participants who wish to stop smoking with the following inclusion and exclusion criteria.

#### 2.4.1. Inclusion criteria.

We will include subjects who:

•are 19 to 70 years old;•have no objection to nicotine patch and AA treatment;•have been smoking more than 10 cigarettes a day;•have attempted or are willing to quit smoking;•use nicotine patches to quit smoking or are willing to receive assistance; and•who voluntarily decided to participate in the clinical trial and provided written consent.

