### 2.7. Procedure

When subjects interested in smoking cessation visit the hospital, a researcher will inform them of the study. This includes information regarding the study purpose, allocation ratio, intervention information (methods and period), expected benefits and risks, and other information required by the Korea Good Clinical Practice for the protection of subjects. Subjects will be informed that they can withdraw from the study at any time with no penalty. If they sign the informed consent form voluntarily, the investigator will collect participants’ demographic characteristics and medical and smoking history, check their vital signs, and determine their eligibility using the inclusion/exclusion criteria. Eligible participants will be assigned to the experimental or control group and undergo 8 treatments (twice weekly visits for 4 weeks, visit 1–8) and 2 follow-ups (1 and 3 months after intervention completion, visit 9–10) (Fig. 2).

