#### 2.10.1. Control group intervention.

A nicotine patch named Nicotinell (manufactured by Lohmann Therapie-Systeme, Andernach, Germany) will be applied for 28 days. Each patch contains 52.5 mg of nicotine and participants will attach this patch and change new patch every day. If there is the patch that the participants have previously used, it will be allowed.

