### 2.11. Outcome measurement

#### 2.11.1. Tobacco consumption and abstinence rate.

The primary outcome will be reductions in daily cigarette smoking, measured in the self-reported number of cigarettes smoked per day. The survey will be completed during visit 1, 4, 8, 9, and 10. The abstinence rate will be determined by the rate of change in the number of cigarettes smoked between the first and last visits (visit 10). Smoking cessation will be biochemically validated by a urine test. The subjects will be asked to submit the urine sample at visit 8 to 10.

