### 2.12. Statistical analysis

We will express continuous variables as means ± standard deviation. For the statistical analysis, we will use paired *t* test for intra-group comparison and a 2-sample *t* test or Wilcoxon rank sum test for comparison between 2 groups. Categorical variables will be expressed as frequencies or percentages and tested statistically with the chi-squared test or Fisher’s exact test. All statistical analyses will be performed with the STATA version 15.0 (STATA Corp, LP. College Station, TX). Significance will be considered at a *P*-value < .05.

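### Section 2.12 compares the change in cigarettes per day by unadjusted tests although visit 1 cigarettes per day is recorded for everyone; ANCOVA on that baseline is more precise at almost no cost (minor)

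*Protocol article*

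**What the plan says.** Section 2.11.1: "The primary outcome will be reductions in daily cigarette smoking, measured in the self-reported number of cigarettes smoked per day". The count is taken at visits 1, 4, 8, 9 and 10. The abstinence rate is described as "determined by the rate of change in the number of cigarettes smoked between the first and last visits (visit 10"). Visit 1 is thus the reference value, and every participant is due to have one.

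Section 2.12 names a paired t test within each group. Between groups it names a 2-sample t "test or Wilcoxon rank sum test for comparison between 2 groups". No covariate enters any comparison.

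Three other statements bear on what the visit 1 value means:
- Section 2.4.1 admits people who "use nicotine patches to quit smoking or are willing to receive assistance" and who "have been smoking more than 10 cigarettes a day".
- Section 2.10.1 adds: "If there is the patch that the participants have previously used, it will be allowed".
- Section 2.7 has the investigator collect "demographic characteristics and medical and smoking history" before allocation, and then: "Eligible participants will be assigned to the experimental or control group and undergo 8 treatments". Visit 1 is therefore the first treatment visit.

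**The concern.** Smokers differ widely in how much they smoke at entry, and what they smoke later is related to it. A plain change score removes this relation with a fixed slope of 1, which is usually too steep. The rank test on change does the same. ANCOVA estimates the slope from the data and also corrects for chance imbalance in visit 1 smoking between two arms of only 20. The baseline is already collected, so the plan gives up precision for no saving.

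A second question concerns the baseline itself. If some participants are already using a patch, their visit 1 count is an on-patch value, while a new starter's is a pre-patch value. That would add spread to the change scores and make each arm's mean change depend on its mix of users.

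**Working it through.** **No plan figure to reproduce.** Section 2.5 takes 12 per group from a pilot-trial rule and raises it to 20 for drop-out. It states no effect size, SD or power. The article also gives no SD of cigarettes per day and no correlation between visits, so these are assumed below.

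**Baseline adjustment.** Let s0 and s1 be the SDs at visit 1 and at follow-up, and r their within-arm correlation.
- Variance of change: s0² + s1² − 2·r·s0·s1.
- Residual variance in ANCOVA: s1²(1 − r²).
- Difference: (s0 − r·s1)², which is never negative. Apart from the cost of estimating the slope, ANCOVA cannot do worse than change, whatever the SDs.

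With s0 = s1, the ratio of standard errors (ANCOVA to change) is √((1 + r)/2). Estimating one slope multiplies the variance by (n − 3)/(n − 4). For n = 40 this is 37/36 = 1.028, or 1.4% in standard error.

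| r | √((1 + r)/2) | with slope cost, 20 per arm | reduction in SE |
|---|---|---|---|
| 0.5 | 0.866 | 0.878 | 12% |
| 0.8 | 0.949 | 0.962 | 4% (5% before the cost) |

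In cigarettes per day, with an assumed SD of 8 at each visit and r = 0.5:
- The SD of change is 8 × √(2 × 0.5) = 8, so the SE is 8 × √(2/20) = 2.53.
- The ANCOVA SE is 8 × √0.75 × √(2/20) × √1.028 = 2.22.
- Simulated trials of 40 with no current patch users give the same pair, 2.53 and 2.22. The gain therefore does not depend on the entry wording.

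**When it would not pay.** Setting (1 + r)/2 × 37/36 = 1 gives r = 72/37 − 1 = 0.946. Only above that does ANCOVA lose to change, and by no more than 1.4%. The same 1.4% is the loss against a plain comparison of follow-up values if visit 1 predicts nothing. Residual degrees of freedom fall from 38 to 37, and the t critical value moves from 2.024 to 2.026. If drop-out leaves 12 per arm, the slope cost is 21/20 = 1.05 in variance, and the reductions become 11% (r = 0.5) and 3% (r = 0.8).

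**Current patch users.** Let q be their share and g the gap in mean change between users and new starters, in within-stratum SDs. Both are assumptions. The variance of unadjusted change is multiplied by 1 + q(1 − q)g².

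| Current users of 40 | q | g | excess variance |
|---|---|---|---|
| 2 | 0.05 | 0.4 to 0.667 | 0.8% to 2.1% |
| 8 | 0.20 | 0.4 | 2.6% |
| 8 | 0.20 | 0.5 | 4.0% |
| 20 | 0.50 | 1.0 | 25% |

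A patch-status term added after visit 1 costs 36/35 = 1.029, or 2.9% in variance. It costs more than the whole excess in the first two rows and nets about 1% in the third. Only the last row, with half the trial already on a patch and a gap of a full SD, gives a real gain. In simulations with an SD of change of 8 and a gap of 4 per day, adding patch status to a model that already had visit 1 changed the SE by about −3% to +1%.

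**Bias.** In 20,000 simulated trials with no treatment effect, the mean between-arm difference was −0.0006 SD (q = 0.2, g = 0.5) and 0.0001 SD (q = 0.5, g = 1). Type I error was 4.9% and 5.4%.

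**The case against.** **The analysis plan may already name ANCOVA.** It is not shown, and covariates are commonly left to it. But Section 2.12 is not silent: it names the between-group tests, and both are unadjusted. The point is about a stated choice, not a missing detail.

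**This is a pilot with no power target.** That is true, so no promised property of the design is lost. It keeps the severity low. It does not remove the case for a more precise estimate from data already in hand.

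**The size of the gain rests on an assumed correlation.** This stands, which is why a range is given. If many participants quit, follow-up counts will also pile up at zero and a linear model with 20 per arm will be approximate. That is a reason to keep the rank test alongside it.

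**A reader might infer more from the entry wording:** that mixing current and new patch users biases the comparison, or that patch status must be adjusted for, stratified on or excluded. The documents do not support this. Admitting current users is one possible reading. The sentence in Section 2.10.1 stands in the product description and may only permit a familiar brand, and the criterion in Section 2.4.1 may mean acceptance of patch-assisted quitting. The smoking threshold most naturally means current smoking, so any current user would still smoke more than 10 a day while on a patch, which limits their number. The same rules apply to both arms, and auricular acupuncture is the only randomised difference. Broad entry also suits a trial that calls itself pragmatic. Recording patch use fits within the smoking history that Section 2.7 already collects.

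**Conclusion.** The point holds as a minor one about efficiency. The unadjusted tests in Section 2.12 are valid, but ANCOVA on visit 1 cigarettes per day would lower the standard error by about 12% at a correlation of 0.5 and by about 4-5% at 0.8. This assumes 20 per arm, equal SDs at the two visits and a roughly linear relation; the correlation itself is not in the documents. The downside is bounded at about 1.4% in standard error.

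The possible entry of current patch users is a matter of wording. It leaves the contrast between arms unbiased, and for modest shares and gaps a patch covariate costs about as much as it returns. Larger effects need many current users and a large gap, and the documents give no support for either. The paired tests within groups would be affected by such a mix, but they are uncontrolled before-after comparisons and hard to attribute to treatment even without it.

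**What to change.** In Section 2.12, state that the primary between-group analysis is a linear model (ANCOVA) of follow-up cigarettes per day on group and visit 1 cigarettes per day, reported as an adjusted difference with its confidence interval. Keep the Wilcoxon rank sum test on change as a sensitivity analysis, and label the within-group paired tests descriptive.

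In Section 2.4.1, a clarifying sentence would help: say that the threshold refers to current smoking, and whether people already using a patch at screening may enter. No exclusion, stratification or patch-status covariate is needed.

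The cost is one degree of freedom and a few sentences. There are no extra visits, measurements or participants.

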#### 2.4.2. Exclusion criteria.

We will exclude subjects who:

•have cardiovascular or lung diseases;•struggle with AA, such as otitis externa;•are reluctant to use acupuncture;•have difficulty attaching nicotine patches and AA due to disease, including severe dermatitis;•receive treatment for mental illness; or•those who struggle with the questionnaire.

### 2.5. Sample size calculation

There have been several studies that investigated the additional efficacy of AA comparing conventional treatment (including NRT and counseling).^[21,23,24]^ However, these studies had some limitations such as using laser AA or a retrospective study. With these reasons, we could not quote fully by previous studies. According to Julious’s suggestion,^[25]^ we determined the appropriate sample size for a 2-parallel study was 12, and in consideration of the drop-out rate, we have decided to recruit 20 participants per group.

### 2.6. Recruitment

This study will be conducted in the Dongguk University Bundang Oriental Hospital. We will draft participants by recruitment posters, local newspapers, and public boards. The posters will contain information about the trial, inclusion/exclusion criteria, intervention methods and period expected benefits and risks, and the contact number.

### 2.7. Procedure

When subjects interested in smoking cessation visit the hospital, a researcher will inform them of the study. This includes information regarding the study purpose, allocation ratio, intervention information (methods and period), expected benefits and risks, and other information required by the Korea Good Clinical Practice for the protection of subjects. Subjects will be informed that they can withdraw from the study at any time with no penalty. If they sign the informed consent form voluntarily, the investigator will collect participants’ demographic characteristics and medical and smoking history, check their vital signs, and determine their eligibility using the inclusion/exclusion criteria. Eligible participants will be assigned to the experimental or control group and undergo 8 treatments (twice weekly visits for 4 weeks, visit 1–8) and 2 follow-ups (1 and 3 months after intervention completion, visit 9–10) (Fig. 2).

**Figure 2. F2:**
[figure not shown]
Study schedule. AA = auricular acupuncture, EQ = EuroQol, FTND = Fagerstrom test for nicotine dependence, MNWS = Minnesota nicotine withdrawal scale, NRT = nicotine replacement treatment, VAS = visual analogue scales.

### 2.8. Randomization and allocation concealment

A randomization sequence will be generated at a ratio of 1:1 by a statistician unrelated to this trial using R software (version 3.5.0; R Foundation for Statistical Computing, Vienna, Austria). The random code will be sealed in opaque envelopes and kept by the code manager. When a subject is eligible, researchers will open the envelope in front of the participant.

### 2.9. Blinding

The additional AA treatment necessitates that the participants and intervention practitioners cannot be blinded. Therefore, outcome assessors will be instructed to ask questions simply and write in detail to record case report form (CRF) and prevent them from conducting intervention to maintain the blinding.

### 2.10. Intervention

Participants in 2 groups will receive the following interventions. Other methods for smoking cessation such as medication will not be allowed during the study period.

#### 2.10.1. Control group intervention.

A nicotine patch named Nicotinell (manufactured by Lohmann Therapie-Systeme, Andernach, Germany) will be applied for 28 days. Each patch contains 52.5 mg of nicotine and participants will attach this patch and change new patch every day. If there is the patch that the participants have previously used, it will be allowed.

#### 2.10.2. Acupuncture intervention.

Based on the control group intervention, participants will receive additional AA treatment. Ear press “T” needles (HL-03; Haeng Lim Seo Won Medical Co., Yeoju-gun, Gyeonggi-do, Republic of Korea) will be inserted at 5 AA points: the shenmen (TF4), lung (CO14), throat (TG3), inner nose (TG4), and endocrine (CO18) points (Table 1; Fig. 3). Previous research indicates that these points have a therapeutic effect.^[27–29]^ Participants will receive treatment twice a week for 4 weeks by a Korean medicine acupuncture and moxibustion specialist. For infection prevention, T needles will be inserted on the left ear in 1, 3, 5, 7 visit while others will be inserted on the right ear in 2, 4, 6, 8 visit.

**Table 1 T1:** Detailed acupuncture treatment based on STRICTA 2010.^[26]^

Item	Detail	
1. Acupuncture rationale	1a) Style of acupuncture (e.g., Traditional Chinese Medicine, Japanese, Korean, Western medical, Five Element, ear acupuncture, etc)	Auricular acupuncture (Ear acupuncture)
	1b) Reasoning for treatment provided, based on historical context, literature sources, and/or consensus methods, with references where appropriate	Based on textbook of acupuncture and moxibustion and previous studies
	1c) Extent to which treatment was varied	All participants will receive nicotine replacement treatment commonly
2. Details of needling	2a) Number of needle insertions per subject per session (mean and range where relevant)	Control group: 0
		Experimental group: 5
	2b) Names (or location if no standard name) of points used (uni/bilateral)	Shenmen (TF4)
		Lung (CO14)
		Throat (TF3)
		Inner nose (TG4)
		Endocrine (CO18)
		Left side at visit 1, 3, 5, 7
		Right side at visit 2, 4, 6, 8
	2c) Depth of insertion, based on a specified unit of measurement, or on a particular tissue level	1mm
	2d) Response sought (e.g., *de qi* or muscle twitch response)	De-qi
	2e) Needle stimulation (e.g., manual, electrical)	T-needles are inserted
	2f) Needle retention time	2–3 d
	2g) Needle type (diameter, length, and manufacturer or material)	T-needles
3. Treatment regimen	3a) Number of treatment sessions	8 sessions
	3b) Frequency and duration of treatment sessions	Twice a week for 4 wk
4. Other components of treatment	4a) Details of other interventions administered to the acupuncture group (e.g., moxibustion, cupping, herbs, exercises, lifestyle advice)	Participants will receive nicotine patch and will be asked to attach 1 patch a day for 4 wk
	4b) Setting and context of treatment, including instructions to practitioners, and information and explanations to patients	Practitioners are instructed to prevent talking with participants
5. Practitioner background	5) Description of participating acupuncturists (qualification or professional affiliation, years in acupuncture practice, other relevant experience)	Korean medicine doctors who are specialist in acupuncture and moxibustion at least 7 yr of experience, or under supervision by a specialist
6. Control or comparator interventions	6a) Rationale for the control or comparator in the context of the research question, with sources that justify this choice	Previous studies about smoking cessation
	6b) Precise description of the control or comparator. If sham acupuncture or any other type of acupuncture-like control is used, provide details as for Items 1 to 3 above	Participants will receive nicotine patch and will be asked to attach 1 patch a day for 4 wk

